# Uni-center, patient-blinded, randomized, 12-month, parallel group, noninferiority study to compare outcomes of 3-row vs 2-row circular staplers for colorectal anastomosis formation after low anterior resection for rectal cancer

**DOI:** 10.1097/MD.0000000000015978

**Published:** 2019-06-14

**Keywords:** anastomotic leakage, colorectal anastomosis, colorectal neoplasms, low anterior resection, rectal cancer, stapled anastomosis, surgical stapling

## Abstract

**Background::**

Colorectal anastomotic leakage (AL) is one of the most serious complications in rectal cancer surgery due to its negative impact on the overall as well as cancer-specific survival. Two-row stapling technique has become standard in low anterior resections (LARs), but has neither alleviated the morbidity, nor reduced the incidence of AL. This is the 1st study that aims to compare the success rate of new 3-row circular staplers compared to that of conventional 2-row staplers in a prospective, randomized clinical trial.

**Methods::**

The THREESTAPLER trial (Clinical Trials NCT03910699) is a prospective, noninferiority, 2-armed, parallel-group, patient and outcomes assessor blinded study with a 1:1 allocation ratio. Colorectal anastomosis will be formed using Ethicon 29 mm Curved Intraluminal Stapler (CDH29A) in the active comparator group, and using Mirus Disposable Circular Stapler 3 Row 29 (MCS-29R3) in the experimental group. The hypothesis states that the incidence of AL in the 3-row stapler group is at least not higher than in the 2-row stapler group. Assuming there is a difference in success rate of 12% and noninferiority margin Δ = 5%, 154 patients will be required to achieve statistical significance. An interim analysis will be performed after recruitment of 20 patients per group to assess safety profile of 3-row circular staplers. The primary endpoint is the rate of AL, documented by imaging studies, assessed with Pearson Chi-squared test and Fisher exact test. The secondary outcomes include severity of AL (A, B, or C), anastomotic bleeding, postoperative complication rate graded with the Clavien–Dindo classification, reintervention rate, stapler dysfunction rate, complications of defunctioning stoma, overall and cancer-specific quality of life, assessed with short form (36) and quality-of-life questionnaire core 30 questionnaires, respectively, fecal incontinence assessed with Cleveland clinic incontinence score form, and manifestation of LAR syndrome. All patients will be monitored for 12 months following the LAR.

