### Objectives

1.2

1.Research hypothesis: 3-row staplers are noninferior to 2-row staplers in colorectal anastomosis formation with respect to anastomotic leakage rate, meaning that AL rate in 3-row-stapled colorectal anastomoses is at least not higher than that of 2-row-stapled anastomoses within 5% noninferiority margin.2.Study objectives2.1.Primary objective: to determine if 3-row staplers are noninferior to 2-row staplers (noninferiority margin Δ = 5%) in the endpoint of anastomotic leakage rate determined by X-ray or computed tomography (CT) scan in subjects undergoing LAR for rectal cancer.2.2.Secondary objectives2.2.1.Key secondary objectives2.2.1.1.Evaluate the incidence of anastomosis-related complications, including anastomotic bleeding and para-anastomotic abscess formation2.2.1.2.Determine the impact of the stapler type on overall and cancer-related quality of life using short form (36) (SF-36) and quality-of-life questionnaire core 30 (QLQ-C30) questionnaires, respectively2.2.2.Other secondary objectives2.2.2.1.Assess the incidence of LAR syndrome (LARS) and level of incontinence during postoperative period in patients with stapled colorectal anastomosis.2.2.2.2.Determine the impact of the stapler type on incontinence, assessed with the Cleveland clinic incontinence score (CCIS) questionnaire.

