### Sample size

2.6

Considering that this is a noninferiority study, the sample size was calculated using 1-sided Blackweder test.^[15]^ According to published data, the incidence of colorectal anastomotic leakage formed standard DST varies from 7% to 25%.^[16]^ Colorectal AL rate after LAR with preventive stoma formation at the study center averages at 18%. The expected incidence of colorectal AL after 3-row suturing device is 30%. The purpose of this study is to obtain preliminary results demonstrating that the outcomes of colorectal anastomosis formation with a 3-row suturing device are noninferior compared to those of a 2-row suturing device. Considering that *α* = 0.05; the statistical power of the study is 80%; the patients are randomized into 2 groups with 1:1 allocation ratio; the noninferiority margin Δ = 5%, the required sample size is 154 patients (77 patients in each of the 2 groups). Thus, if there is a true difference in favor of the experimental treatment of 12% with respect to AL rate, then 154 patients are required to be 80% sure that the upper limit of a 1-sided 95% confidence interval will exclude a difference in favor of the standard group of more than 5%.

In order to conduct an interim analysis to assess the safety of 3-row suturing devices for the formation of a colorectal anastomosis, 20 patients will be included in each group. Given a 10% probability of patients leaving the study, it is necessary to recruit 22 patients in each group. Thus, a sample of 44 patients (22 in each of the 2 comparison groups) should allow for a reliable preliminary assessment of the safety and feasibility of the use of 3-row suturing devices for the formation of colorectal anastomosis.

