#### Statistical methods

2.9.3

An intention to treat analysis will be performed. The quantitative variables will be described as means and standard deviations or as medians, interquartile range, and range, as appropriate. Categorical variables will be described in absolute numbers and percentages. The statistical analysis of the quantitative variables, with independent groups will be performed with the parametric Student *t* test, provided that its conditions for application are met. Otherwise, the nonparametric Mann–Whitney *U* test will be used. Statistical analysis for categorical variables will use the Pearson Chi-squared test or the Fisher exact test. Specifically, the above methods will be used to compare the 2 groups in terms of baseline characteristics in order to assess whether the randomization has been effective. Overall and recurrence-free survival rates will be estimated using the Kaplan–Meier method, and the log-rank test will be used to compare overall survival between the 2 groups. Differences between groups are considered significant at *P* = .05.

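### The primary noninferiority endpoint is assigned to chi-squared and Fisher tests of equality, which never use the 5% margin

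*Protocol article*

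**What the plan says.** The primary objective (section 1.2) is "to determine if 3-row staplers are noninferior to 2-row staplers (noninferiority margin Δ = 5%) in the endpoint of anastomotic leakage rate". Section 2.6 sizes the trial for that question: "the sample size was calculated using 1-sided Blackweder test", with α = 0.05, 80% power, a 5% margin and 77 patients per arm (154 in all). It explains the target as 80% assurance that the "upper limit of a 1-sided 95% confidence interval will exclude a difference in favor of the standard group of more than 5" percent.

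The analysis is described differently. The abstract (Methods) states: "The primary endpoint is the rate of AL, documented by imaging studies, assessed with Pearson Chi-squared test and Fisher exact test". Section 2.9.3 says: "Statistical analysis for categorical variables will use the Pearson Chi-squared test or the Fisher exact test". It adds: "Differences between groups are considered significant at" P = .05. That section does not mention the margin, a confidence interval for the difference in AL, or a rule for declaring noninferiority.

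**The concern.** Pearson's chi-squared and Fisher's exact test, in their usual form, have as null hypothesis that the two AL rates are equal. The trial's null hypothesis is that the 3-row rate exceeds the 2-row rate by at least 5 points. No P value from the named tests answers that question, whichever way it falls:

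- A non-significant result does not show that an excess of 5 points or more has been ruled out. In a trial of this size it is likely even when the 3-row device is clearly worse.
- A significant result in favour of the 3-row device would be sufficient, but it demands superiority, and the trial was not sized for that.

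At stake is the trial's main conclusion about a serious complication. A device outside the margin could be reported as not different, and one inside it could be reported as having failed.

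**Working it through.** **Inputs.** Margin 5 points (1.2, 2.6); α = 0.05 in a one-sided calculation, power 80%, 77 per arm (2.6); AL rates of 18% and 30%, a 12-point difference (2.6); tests and P = .05 (abstract, 2.9.3). Section 2.9.3 gives no sidedness, so two-sided testing is assumed unless stated.

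**1. Which test was the trial sized for?** Use success rates of 70% (2-row) and 82% (3-row), that is, the 12 points favouring the 3-row device:

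n per arm = (0.70 × 0.30 + 0.82 × 0.18) × (1.645 + 0.842)² / (0.05 + 0.12)² = 0.3576 × 6.18 / 0.0289 = 76.5, so 77 per arm and 154 in total.

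This reproduces the plan's figure, and the margin is part of the formula. A two-sided chi-squared test of 18% against 30% would need

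n per arm = [1.960 × √(2 × 0.24 × 0.76) + 0.842 × √0.3576]² / 0.12² ≈ 198.

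So the sample size belongs to the margin test and not to the tests named for analysis.

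**2. How do the tests behave at 77 per arm?** All pairs of binomial counts were enumerated exactly. The margin criterion is met when d + 1.645 × √[p₁(1−p₁)/77 + p₂(1−p₂)/77] < 0.05, where d is the 3-row minus the 2-row AL proportion (Wald limit). Chi-squared is uncorrected; both equality tests are two-sided at 0.05.

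| True AL, 2-row / 3-row | Chi-squared non-significant | Fisher non-significant | Margin criterion met |
|---|---|---|---|
| 18% / 23% (at the margin) | 88% | 92% | 5.0% |
| 18% / 28% | 69% | 75% | 0.9% |
| 18% / 30% | 58% | 65% | 0.4% |
| 30% / 18% (scenario that reproduces 154) | 58% | 65% | 80% |

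In the last row, chi-squared is significant in favour of the 3-row device in 42% of trials and Fisher in 35%.

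**3. Does the two-sided assumption matter?** If chi-squared is made one-sided against a worse 3-row device (significant when z > 1.645), the same enumeration gives non-significance in 81% of trials at 18% / 23% and 46% at 18% / 30%. The picture does not change.

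**4. Single results, 2-row against 3-row.**

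- 14/77 against 24/77 (18.2% and 31.2%): chi-squared P = .062, Fisher P = .092. The one-sided 95% upper limit is 0.130 + 1.645 × 0.0687 = 0.243, or +24.3 points. No significant difference, and far from noninferior.
- 14/77 against 14/77: P = 1.0 on both tests. The upper limit is 0 + 1.645 × 0.0622 = 0.102, or +10.2 points. Identical results still do not show noninferiority.
- 23/77 against 14/77 (29.9% and 18.2%): chi-squared P = .090, Fisher P = .131. The upper limit is −0.117 + 1.645 × 0.0682 = −0.005, or −0.5 points. Not significant, yet noninferiority is met.

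**The case against.** The best defence is that the right criterion is already in the document: section 1.2 carries the margin and section 2.6 states the one-sided 95% limit. On that view this is an inconsistency to reconcile, not a trial without a valid test. That is a fair description of the whole document. It does not rescue the abstract and 2.9.3, because the abstract assigns other tests to this endpoint by name. Nor is this detail left to an unseen analysis plan: the article states a method, and the method does not fit the hypothesis.

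Four further points stand as limits on the claim:

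- The protocol nowhere says that P > .05 will be read as noninferiority. The 88% and 58% are error rates only under that reading. If significance in favour of the 3-row device were required instead, the false-positive rate at the margin would be about 0.3%, and the cost would be lost power.
- Two-sidedness is an assumption, because 2.9.3 is silent on it.
- The 80% and 42% need the 12 points to favour the 3-row device. Section 2.6 says so in its closing explanation, but the rates it prints point the other way: "Colorectal AL rate after LAR with preventive stoma formation at the study center averages at 18" percent, with 30% expected for the 3-row device. That contradiction is a separate matter.
- The abstract joins the two tests with *and*, section 2.9.3 with *or*. This is a minor looseness and does not carry the point.

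**Conclusion.** The concern holds. The analysis stated for the primary endpoint does not test the noninferiority hypothesis, and it differs from the criterion on which the 154 patients were based. This must be corrected, because it decides the main conclusion.

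The size depends on how the P value would be used, which the protocol does not say. If non-significance counts as success, the false-positive rate at the margin is 88% with chi-squared, or 92% with Fisher, against an intended 5%. If significance counts as success, the chance of success in the scenario behind the sample size falls from 80% to 42% or 35%. These figures assume 77 analysed patients per arm, uncorrected chi-squared, two-sided tests at 0.05 and a Wald limit for the margin criterion. That no equality test can establish the 5-point claim rests on none of these assumptions.

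**What to change.** In section 2.9.3 and the abstract, define the primary analysis as the risk difference in AL, 3-row minus 2-row, with the one-sided 95% upper limit already described in 2.6 (the upper bound of a two-sided 90% interval). Declare noninferiority only if that limit is below 5 percentage points. A score interval such as Miettinen–Nurminen or Newcombe would serve, and the choice can be left to the analysis plan. Keep chi-squared and Fisher for other categorical outcomes and for a superiority test of AL once noninferiority has been shown.

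This is a change of wording, with no added data or patients. It does not settle the direction of the 18% and 30% rates in 2.6, which has to be reconciled separately. The margin criterion has its 80% power only if the 12 points favour the 3-row device. With equal rates of 18%, 77 per arm would meet it in about 20% of trials, and 80% power would need about 731 per arm.

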**Discussion::**

This is the 1st prospective randomized trial to assess the safety profile of 3-row staplers for colorectal anastomosis after LAR for rectal cancer. It may provide evidence of feasibility of 3-row circular staplers in LAR with respect to short-term and long-term patient outcomes.

Trial registration: NCT03910699 on 10 April 2019

## Introduction

1

### Background and rationale

1.1

Anastomotic leakage (AL) is one of the most serious complications of low anterior resection (LAR) with a sphincter-preserving total mesorectal excision (TME) for rectal cancer. Despite the refinement of the surgical techniques used in rectal cancer surgery, AL rate remains high with a reported value in a recent systematic review of 6.3%.^[1]^ However, a retrospective study assessing the rate of AL after LAR with double-stapling technique (DST) has reported AL rate of 12.3%.^[2]^ Additionally, a 2010 systematic review that included a broader patient population has demonstrated AL rate of 11%.^[3]^ Thus, the incidence of AL varies widely as it has a multifaceted etiology due to a large number of risk factors. AL has a detrimental effect on both short-term and long-term patient outcomes due to high reintervention and a decreased survival rate. A recent systematic review has shown an association between AL and a higher chance of local cancer recurrence, as well as with lower overall and cancer-specific survival.^[4]^ The increase in cancer recurrence can be explained by “extraluminal tumor implantation” by free malignant cells that may be present in anastomotic line. AL is also associated with higher costs due to high reintervention rate: according to retrospective national cohort study conducted by Boström et al in Sweden that included 6948 patients within the period from 2007 to 2016, 693 of patients (10.0%) experienced AL, and 294 (4.2%) underwent reintervention due to AL.^[5]^

Two-row staplers have long been standard in colorectal in general surgery; however, 3-row stapling devices have also emerged. Although circular staplers have simplified low and ultra-low anastomoses formation,^[6]^ their usage did not decrease the risk of AL. Moreover, the efficacy and safety of 3-row staplers has only been briefly addressed in the existing literature.^[7,8]^ Previous studies have almost exclusively focused on comparison of different techniques of colorectal anastomosis formation,^[9,10]^ whereas the research assessing different types of stapled anastomoses is mostly limited to single- vs double-stapled techniques.^[11,12]^ Up to date, no previous research has investigated the efficacy of 3-row circular staples for colorectal anastomoses formation compared to that of conventional 2-row staplers. However, retrospective observational study by Foo et al has compared the outcomes of 3- and 2-row linear stapler usage for ileocolic anastomoses formation. Notably, the reoperation rate in 3-row staplers group was found to be significantly lower in the experimental group (5.9%) compared to 1.8% in the control group *(P* *=* .049).^[7]^ Thus, a lower morbidity rate was demonstrated in tri-staplers group. Despite the indefinite results, the findings of the study suggest further need for evaluation of efficacy of 3-row staplers for low colorectal anastomoses formation in a prospective randomized controlled clinical trial (Table 1).

**Table 1 T1:**
[figure not shown]
Data set.

The data on comparison of different types of circular staplers for colorectal anastomosis formation are scarce. The results of a Swedish trial suggest that the type of stapler is an independent risk factor of AL.^[13]^ Therefore, our study aims to investigate safety and efficacy of 3-row circular stapler (Mirus Disposable Circular Stapler 3 Row 29 [MCS-29R3]) as compared to standard 2-row circular stapler (Ethicon 29 mm Curved Intraluminal Stapler [CDH29A]) that have been conventionally used in LARs for over 10 years. All foreseeable patient risks are attributed the operation remain similar in both control and experimental groups. Possible anastomosis-related complications include anastomotic leak, anastomotic bleeding, anastomotic stricture, para-anastomotic abscess.

### Objectives

1.2

1.Research hypothesis: 3-row staplers are noninferior to 2-row staplers in colorectal anastomosis formation with respect to anastomotic leakage rate, meaning that AL rate in 3-row-stapled colorectal anastomoses is at least not higher than that of 2-row-stapled anastomoses within 5% noninferiority margin.2.Study objectives2.1.Primary objective: to determine if 3-row staplers are noninferior to 2-row staplers (noninferiority margin Δ = 5%) in the endpoint of anastomotic leakage rate determined by X-ray or computed tomography (CT) scan in subjects undergoing LAR for rectal cancer.2.2.Secondary objectives2.2.1.Key secondary objectives2.2.1.1.Evaluate the incidence of anastomosis-related complications, including anastomotic bleeding and para-anastomotic abscess formation2.2.1.2.Determine the impact of the stapler type on overall and cancer-related quality of life using short form (36) (SF-36) and quality-of-life questionnaire core 30 (QLQ-C30) questionnaires, respectively2.2.2.Other secondary objectives2.2.2.1.Assess the incidence of LAR syndrome (LARS) and level of incontinence during postoperative period in patients with stapled colorectal anastomosis.2.2.2.2.Determine the impact of the stapler type on incontinence, assessed with the Cleveland clinic incontinence score (CCIS) questionnaire.

### Trial design

1.3

THREESTAPLER study is a prospective, randomized, controlled, patient and outcomes assessor blinded, uni-center, noninferiority, parallel group, 2-arm trial with 1:1 allocation ratio. Randomization will be performed using block method after intraoperative eligibility assessment.

## Methods

2

### Study setting

2.1

The study will be conducted at the Clinic of Colorectal and Minimally Invasive Surgery of the Sechenov University Hospital N. 2 in Moscow, Russia. Patients with colorectal cancer comply a significant part of patient body; on average, 150 patients are diagnosed with and treated for rectal cancer per year, the interventions include open, laparoscopic, and robotic approaches. Thus, in this case, a single-center design can assure sufficient patient recruitment.

### Eligibility criteria

2.2

To be eligible for randomization, an individual must comply with all of the following criteria:

Inclusion criteria

1.1.Provision of signed and dated informed consent form1.2.Stated consent to comply with all study procedures and availability for the duration of the study1.3.Male or female1.4.For females of reproductive potential: not pregnant at the time of screening1.5.For males of reproductive potential: use of condoms or other methods to ensure effective contraception with partner1.6.Histologically proven primary rectal adenocarcinoma located within 5 to 15 cm from anal verge not involving internal and/or external sphincter muscle

Exclusion criteria

2.1.Preoperative and intraoperative2.1.1.Current use of antiplatelet drugs, acetylsalicylic acid, or anticoagulants within 7 days prior to intervention2.1.2.Unresectable tumor, inability to perform a TME with colorectal anastomosis, inability to complete R0 resection, or presence of T4b tumor necessitating a multiorgan resection2.1.3.Inability to save the left colic artery2.1.4.Diameter of rectal lumen is unable to contain the working part of the stapler2.1.5.Infection requiring antibiotic treatment within 30 days prior to intervention2.1.6.Anal incontinence prior to surgery (Wexner continence grading scale ≥10)

Postoperative

2.2.1.Inability to complete all the trial procedures2.2.2.Death due to causes unrelated to anastomotic leak in early postoperative period2.2.3.Patient wants to withdraw from the clinical trial

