#### Primary outcome measure

2.4.1

The primary outcome measure is the difference between the 2 groups in the incidence of colorectal anastomosis leakage documented with an X-ray and/or CT scan in the time period between the LAR and stoma reversal surgery.

As proposed by the International Study Group of Rectal Cancer, AL is defined as a “defect of the intestinal wall integrity at the colorectal or coloanal anastomotic site (including suture and staple lines of neorectal reservoirs) leading to a communication between the intra- and extraluminal compartments,” or presence of “a pelvic abscess close to the anastomosis.”^[14]^ In context of primary outcome analysis only presence or absence of diagnosed AL (dichotomous aggregation method) from the day of intervention to preventive stoma reversal will be considered. The timeframe for the primary outcome measure is defined as the period between the initial surgery and stoma reversal, which usually takes place at 4 to 6 weeks after LAR, and may differ significantly between subjects due to variability of AL presentation and symptoms. Additionally, AL may be asymptomatic and discoverable only with imaging studies, which are only necessary to ensure the safety of stoma reversal surgery.

All patients undergoing LAR with stapled colorectal anastomosis formation will be treated according to intervention protocol described in the corresponding section. The patients’ status will be monitored twice a day during rounds. AL has a multifaceted clinical course and has no pathognomonic features; it may be asymptomatic and require no intervention, or it can lead to serious complications, such as peritonitis and sepsis. The clinical signs of AL include the following:

1.General1.1. Fever (≥38.0°C)1.2. Tachycardia (≥100/min)1.3. Increased respiratory rate (≥30/min)1.4. Renal insufficiency (<30 mL/h or <700 mL/d)1.5. Altered mental status (agitation/lethargy, GCS < 15)1.6. Deterioration of overall clinical condition1.7. Peritonitis (clinical signs of abdominal guarding, rebound tenderness, abdominal pain worsening with movement, etc)1.8. Sepsis (qSOFA ≥ 2)2.Local2.1. Bowel obstruction2.2. Abnormal drain content (purulent/turbid/air)2.3. Purulent or fecal vaginal discharge (rectovaginal fistula)2.4. Abdominal pain other than wound pain2.5. Fascial dehiscence3.Laboratory signs include:3.1. Leukocytosis3.2. C-reactive protein elevation

There are several ways in which AL can be diagnosed in the investigated subjects (Fig. 1).

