#### Allocation

2.8.1

Participants will be randomly assigned to either control or experimental group with a 1:1 allocation ratio using fixed block randomization with a computerized random number generator. The block size equals at least 4 and will be unknown to the principal investigator, outcomes assessor and the operating surgeon. Because the possibility of making a stapled anastomosis will only be determined intraoperatively by the operating surgeon with respect to exclusion criteria precluding stapled anastomosis formation, all subjects will be allocated intraoperatively.

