#### Data collection methods

2.9.1

All data will be collected prospectively using eCRFs designed for this trial. The reasons for withdrawal will be documented. The investigator will attempt to contact each participant at least 3 times during each follow-up window before declaring them lost for observation. The study exit form will be recorded in the eCRF. All prior data will be analyzed within the research.

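### Three postoperative exclusion criteria act only after intraoperative randomisation, which conflicts with the unqualified intention-to-treat analysis and leaves the denominator for anastomotic leakage unsettled

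*Protocol article*

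**What the plan says.** Section 2.2 (Eligibility criteria) opens with "To be eligible for randomization, an individual must comply with all of the following criteria". Its exclusion list then has a postoperative part with three items:

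- 2.2.1: "Inability to complete all the trial procedures"
- 2.2.2: "Death due to causes unrelated to anastomotic leak in early postoperative period"
- 2.2.3: "Patient wants to withdraw from the clinical trial"

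Section 2.8.1 (Allocation) states that "all subjects will be allocated intraoperatively", and section 1.3 (Trial design) agrees. Section 2.9.3 (Statistical methods) says "An intention to treat analysis will be performed". It names no modified set and makes no exception. Section 2.9.1 (Data collection methods), after describing withdrawal, loss to follow-up and the exit form, adds "All prior data will be analyzed within the research".

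**The concern.** A criterion that can be met only after surgery cannot govern eligibility for a randomisation that happens during surgery. Applied as written, it takes randomised patients out of the comparison, and intention to treat rules that out.

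The removals need not be neutral. The primary endpoint closes at stoma reversal, usually 4 to 6 weeks after resection (section 2.4.1), but the trial's procedures include questionnaires up to 12 months (section 2.4.2). Item 2.2.1 sets no time horizon. Read literally, it could exclude a patient whose leak was documented early but who missed a later visit. Section 2.4.1 also says that the time to reversal "may differ significantly between subjects due to variability of AL presentation and symptoms", so a link between leak and completion is plausible. Item 2.2.2 requires a judgement of cause of death after randomisation. By the protocol's own account a leak may be silent and found only on imaging, so a patient who dies before the pre-reversal X-ray may never have had leak status established.

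At stake is the denominator, and possibly the numerator, of the primary noninferiority comparison.

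**Working it through.** **The passages side by side.** Allocation is intraoperative (1.3, 2.8.1). The three items are postoperative (2.2). Every patient who meets one has therefore been randomised. Section 2.9.3 keeps all randomised patients and section 2.2 excludes some of them. Section 2.9.1 speaks of data already collected but not of the analysis set. The three statements do not fix a single denominator.

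**The plan's own figure.** With one-sided α = 0.05, 80% power, a 12-point advantage and a 5-point margin (section 2.6):

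n = (1.645 + 0.842)² × (0.30×0.70 + 0.18×0.82) / (0.05 + 0.12)² = 6.185 × 0.3576 / 0.0289 = 76.5, so 77 per arm and 154 in total.

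The stated size reproduces, with 30% AL taken for 2-row and 18% for 3-row. Section 2.6 labels the two rates the other way round. That is a separate matter and does not affect this point.

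**Can one exclusion change the verdict?** Section 2.6 decides on the upper limit of a one-sided 95% confidence interval against 5 points. It does not name an interval method; I assume unpooled Wald. With p₂ and p₃ the 2-row and 3-row AL proportions:

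d = p₃ − p₂; SE = √[p₂(1−p₂)/n₂ + p₃(1−p₃)/n₃]; U = d + 1.645 × SE.

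The counts below are assumed.

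- All randomised, 14/77 vs 11/77: d = 0.14286 − 0.18182 = −0.03896; SE = 0.05935; U = −0.03896 + 0.09763 = 0.0587, or 5.9 points. Noninferiority fails.
- One leaking 3-row patient excluded, 14/77 vs 10/76: d = 0.13158 − 0.18182 = −0.05024; SE = 0.05861; U = −0.05024 + 0.09641 = 0.0462, or 4.6 points. Noninferiority passes.

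**What systematic exclusion could do.** Take true AL rates exactly at the margin: 18% (the centre's rate) and 23%. Let a fraction f of leak patients and g of non-leak patients be removed. The expected observed rate is p(1−f) / [p(1−f) + (1−p)(1−g)]. For f = 0.30 and g = 0.05 in both arms: 0.126/0.905 = 13.9% and 0.161/0.8925 = 18.0%, a difference of 4.1 points instead of 5.0. With d* and SE* computed on the patients left from 77 per arm, type I error is Φ[(0.05 − d*)/SE* − 1.645]. All fractions are assumptions.

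| Leak patients removed (2-row / 3-row) | Non-leak removed | Difference (points) | One-sided type I error |
|---|---|---|---|
| 10% / 10% | 10% | 5.0 | 5.0% |
| 20% / 20% | 5% | 4.5 | 5.9% |
| 30% / 30% | 5% | 4.1 | 6.6% |
| 50% / 50% | 5% | 3.2 | 9.2% |
| 5% / 20% | 5% | 2.1 | 11.5% |
| 5% / 30% | 5% | 0.0 | 19.0% |

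The first row shows that removal unrelated to leak and arm does not bias the comparison. It does cost precision: with 10% removed, 77 × 0.90 = 69.3 remain per arm and power on the planning assumptions falls from 80.2% to 76.5%.

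**The case against.** The strongest reply is that the postoperative list is merely mislabelled. Section 2.9.1 says reasons for withdrawal are documented and data collected earlier are analysed. Together with the intention-to-treat sentence, this supports reading the three items as reasons for stopping follow-up. No passage says outright that these patients leave the analysis set. That reading is reasonable, and it is where the protocol should end up. But section 2.9.1 does not withdraw the exclusion criteria or settle the denominator, so the conflict stands.

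Some stronger readings are tempting and are not supported:

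- A reader might infer that all patients who die are removed. Item 2.2.2 covers only deaths unrelated to leak in the early period, which section 2.3.4 defines as up to 30 days. Leak-related and later deaths are outside it. The protocol states outcome-assessor blinding and keeps stapler type out of the eCRF (section 2.8.2), but does not say who judges cause of death.
- A reader might apply the 10% loss to 77 per arm. Section 2.6 states it only for the interim sample.
- A reader might argue from point estimates that losing four leaking 3-row patients creates noninferiority, since 14/77 vs 18/77 (5.2 points) becomes 14/77 vs 14/73 (1.0 point). The decision rests on the upper limit: 0.05195 + 1.645 × 0.06525 = 15.9 points before and 0.00996 + 1.645 × 0.06368 = 11.5 points after. Both exceed 5, so the trial fails either way.
- A reader might fault the absence of an imputation rule or a per-protocol analysis. These are commonly left to a statistical analysis plan, which is not shown, so their absence is no finding.

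**Conclusion.** The protocol is wrong as written on this point. It excludes patients for events that can occur only after randomisation while promising an unqualified intention-to-treat analysis, and nothing else in it resolves which rule sets the AL denominator. The contradiction rests on the text alone and needs no assumption.

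It would go too far to say that the AL comparison is biased. Bias arises only if exclusion is related to leak or arm. That is plausible here but not shown, and with no exclusion rates in the documents its size is unknown. The boundary example (5.9 against 4.6 points) and the type I error figures (5.9% to 9.2% with equal removal of leak patients, about 11% to 19% with heavier removal in the 3-row arm) rest on assumed counts, assumed fractions and normal approximations. Another interval method would shift the limits somewhat. They show that the choice of denominator can matter to the verdict, not that it will.

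**What to change.** Remove 2.2.1 to 2.2.3 from the exclusion criteria and restate them as reasons for ending follow-up. In section 2.9.3, say that every randomised patient is analysed in the allocated arm and that any AL recorded before withdrawal, death or non-completion counts as an event. Reword the sentence in section 2.9.1 to match. As optional support, add a sensitivity analysis for patients whose AL status was never assessed.

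Settle this before outcome data are examined by arm, including at the interim analysis. The cost is a short amendment and slightly more analysis work. The result may be less favourable to the 3-row stapler than one based on patients who completed everything.
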